### Study timeline

Study preparation will take 3 months, enrollment will take 3 years, and data collection will be completed within 4.5 years.

### Sample size

Sample estimation is based on the effect of RFB+VSOP combined intervention on two primary outcomes (ANS flexibility and cognition/IADL) by comparing to other groups (IR+VSOP control and IR control only). Literature indicates the following information related to deciding the effect size: (1) a moderate to large effect (using Hedges’ *g* = 0.83) of HRVB (including RFB) on stress regulation measures [17], (2) a small to moderate effect of VSOP on cognition, (3) correlation between ANS measures (*χ*^2^ = 11.70, *r* = 0.44) [7, 64], and (4) correlations between ANS measures and cognition (pooled *r* = 0.16) [65]. We estimate alpha = 0.025 (correct for two comparisons: combined intervention group with VSOP+IR control, as well as with the IR control group), and 3 measurement time points: baseline, post-intervention assessment, and 12-month follow-up. A sample size of 96 will be able to detect a small effect (*d* = 0.20). We further estimate a 20% attrition rate at the 12-month follow-up (in another local longitudinal study of cognitively healthy older adults [name] conducted [66], the attrition rate was less than 20% for up to a 5-year follow-up), and we will use a sample size of 114 (*n* = 38 per group).

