**Objective:**

The goal of the study is to test whether improving autonomic nervous system (ANS) flexibility via a resonance frequency breathing (RFB) training will strengthen the effects of a visual speed of processing (VSOP) cognitive training on cognitive and brain function, and slow the progress of dementia in older adults with mild cognitive impairment (MCI).

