
The objective of the study is to test whether adding RFB to the vision-based speed of processing training (VSOP)—the most widely tested cognitive training among older adults [24–27]—will enhance the training effects of VSOP by strengthening adaptation capacity that affords greater adaptive learning and neuroplasticity, and slow the progress of dementia in MCI. We will examine long-term effects of the combined intervention on ANS flexibility and cognitive and functional capacity and explore potential long-term effects of the combined intervention on neurodegeneration. Relevant hypotheses include the following: the combined intervention will have a greater effect on CAN and HRV—indicators of autonomic flexibility—as well as cognition and everyday function, and less neurodegeneration, compared to control groups throughout the follow-up period; improvements in ANS flexibility will predict improvement on cognition and everyday function and slower neurodegeneration over time.

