#### Set-up of the IR+VSOP control group and IR-only group

For the IR+VSOP control group, the control IR strategy will be used, the set-up of which will be the same as the combined intervention group with IR replacing RFB. Participants randomized to the IR-only group will receive weekly in-person check-in visits and perform daily 10-min IR, so that the number of treatment contacts (though not duration) will be equivalent.

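### Alpha is split equally between the two control comparisons, although only RFB+VSOP v IR+VSOP tests the stated objective, so that comparison loses power

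*Protocol article*

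**What the plan says.** All places are in the protocol article.

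- **Objective.** The abstract asks whether RFB "will strengthen the effects of a visual speed of processing (VSOP) cognitive training on cognitive and brain function". The Introduction asks whether adding RFB to VSOP "will enhance the training effects of VSOP by strengthening adaptation capacity". The Discussion repeats the idea, with VSOP alone as the reference.
- **Hypothesis.** The Introduction expects a greater effect of the combined intervention "compared to control groups throughout the follow-up period". It does not say whether one control or both must be beaten.
- **Arms.** IR+VSOP is a control "the set-up of which will be the same as the combined intervention group with IR replacing RFB". The IR-only arm has relaxation without VSOP, with the number of contacts matched but not their duration.
- **Alpha.** The Sample size section uses 0.025 to "correct for two comparisons: combined intervention group with VSOP+IR control, as well as with the IR control group". The same paragraph lists, among its planning inputs, "a small to moderate effect of VSOP on cognition". It gives no VSOP effect on ANS flexibility, the other primary outcome.
- **Analysis.** The Data analysis section calculates an effect size for RFB+VSOP and one for IR+VSOP, each against the attention control, and compares the two to judge the additive effect. It states no alpha, order of testing or success rule.

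**The concern.** The two comparisons have different null hypotheses. For RFB+VSOP v IR+VSOP, the null is that RFB adds nothing to VSOP, which is the trial's question. For RFB+VSOP v IR-only, the null is that RFB and VSOP together add nothing to relaxation. The Sample size section gives both the same standing and the same share of alpha.

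Two things are at stake. First, the comparison that answers the objective is tested at half the implied overall 0.05, and so loses power. Second, for cognition, the IR-only comparison can be significant through VSOP without any contribution from RFB. If the two results are reported as equal primary comparisons, a reader could credit RFB with an effect that belongs to VSOP.

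**Working it through.** **1. The stated alpha.** 0.05 / 2 = 0.025. The figure reproduces. The overall 0.05 is implied, not stated.

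**2. What each comparison contains.** Take the IR-only arm as zero, write V for the VSOP effect and R for the gain from RFB in place of IR, and assume the effects add up.
- RFB+VSOP v IR+VSOP: (V + R) − V = R
- RFB+VSOP v IR-only: (V + R) − 0 = V + R

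If R = 0, the second comparison still estimates V.

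**3. Does the objective need a split?**
- If both controls must be beaten, each test can run at the full alpha. The familywise error for that joint claim is still controlled, so no split is needed.
- If the RFB question comes first, a fixed sequence gives it the full alpha and still controls the familywise error over the two comparisons.
- If each comparison is a separate claim that may succeed alone, some correction is needed and the equal split is a valid one.

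**4. Power lost by the RFB comparison.** Inputs: 38 per arm and 20% attrition from the Sample size section, so 38 × 0.8 = 30.4, taken as 30. Assumptions: baseline-adjusted mean of two follow-ups, equal between-visit correlation rho, unit SD, normal theory. The follow-ups are two because the sample size counts three time points including baseline.

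v = (1 + rho)/2 − rho²; SE = √(2v/30); power = Φ(d/SE − z), with z = 2.241 at 0.025 and 1.960 at 0.05.

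- rho = 0.5: v = 0.75 − 0.25 = 0.50 and SE = 0.183. At d = 0.35, d/SE = 1.917. Power is Φ(−0.324) = 37% at 0.025 and Φ(−0.043) = 48% at 0.05.
- rho = 0.78: v = 0.89 − 0.608 = 0.282 and SE = 0.137. At d = 0.35, d/SE = 2.554. Power is 62% at 0.025 and 72% at 0.05.

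The value 0.78 is the lower test-retest reliability that the Measures section quotes for the executive function battery. It serves only as a plausible higher correlation.

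A simpler model gives the same picture: one follow-up, no baseline adjustment, and 96 / 3 = 32 per arm, so SE = √(2/32) = 0.25. At d = 0.35, power is 20.0% at 0.025 and 28.8% at 0.05. At d = 0.50 it is 40.5% and 51.6%. For 80% power, the required n changes by the factor ((1.960 + 0.842)/(2.241 + 0.842))² = 0.826, about 17% fewer at the full alpha.

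**5. Chance that RFB+VSOP beats IR-only when RFB is inert (cognition).** Two-sided 0.025, 32 per arm, one follow-up. Unadjusted SE = 0.25. With baseline adjustment at an assumed correlation of 0.7, SE = 0.25 × √(1 − 0.49) = 0.179. Chance = Φ(d/SE − 2.241).

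| Assumed VSOP effect d | Unadjusted | Baseline-adjusted |
|---|---|---|
| 0.20 | 7.5% | 13.1% |
| 0.35 | 20.0% | 38.9% |
| 0.50 | 40.5% | 71.2% |

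In the same scenarios, the chance that RFB+VSOP beats IR+VSOP is 0.025 / 2 = 1.25%.

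**The case against.** **Either win counts as success.** A reader might infer this from the correction and conclude that the trial would be declared positive for RFB on VSOP alone. The documents do not support that. No section states a success rule, and nothing says that a win over IR-only will be read as evidence for RFB. An order of testing may also sit in an analysis plan that is not shown. This objection stands, so the point rests only on the alpha allocation that the article does fix.

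**The Data analysis section already uses IR+VSOP for the additive effect.** This is true and it reduces the risk of misreading. If the same standard deviation divides both effect sizes, the IR-only terms cancel and the RFB+VSOP v IR+VSOP difference remains. But this is a comparison of effect sizes, with no decision rule, and it leaves the alpha allocation as it was.

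**The split is legitimate and buys something.** The package against relaxation and the increment from RFB are distinct questions, and the equal split keeps the first confirmatory if the second fails. This also stands: 0.025 is not an error. Still, no stated objective rests on the IR-only comparison alone.

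**The false-support argument is broader than the evidence.** It is tempting to extend it to both primary outcomes or to call a VSOP-driven win likely. Neither is supported. The Sample size section expects a VSOP effect on cognition only, and at d = 0.20 the chance is 7.5% to 13.1%.

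**The calculations simplify the planned model.** The Data analysis section plans a mixed model with categorical visits, including 6 months. The percentages are therefore illustrations of size, not predictions for that model.

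**Conclusion.** The point holds as a mismatch between the alpha allocation and the objective. The 0.025 is arithmetically right and controls the familywise error over the two comparisons.

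- **Power, both primary outcomes.** At d = 0.35 and 30 per arm, the RFB comparison falls from 48% to 37% (rho 0.5) or from 72% to 62% (rho 0.78). That is about 10 percentage points, with d and rho assumed. If the hypothesis means that both controls must be beaten, the loss buys nothing.
- **Interpretation, cognition only.** With RFB inert, the IR-only comparison rejects in favour of the combined arm with a chance of about 7% to 71%, for assumed VSOP effects of 0.2 to 0.5 and a baseline correlation between none and 0.7. A win on it alone is not evidence for RFB.

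The plan should be changed, but this does not show that it would declare success for RFB on the wrong comparison.

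**What to change.** In the Sample size and Data analysis sections, for each primary outcome:

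1. Name RFB+VSOP v IR+VSOP as the test of the objective.
2. Test it first, at the full alpha available to that outcome.
3. Test RFB+VSOP v IR-only only if the first test succeeds, at the same alpha (fixed sequence).
4. State that the IR-only comparison supports only a claim about the whole package against relaxation.

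This changes wording only and needs no more participants. The cost is that the IR-only comparison becomes supportive whenever the first test fails. At 48% power that would be about half the time (1 − 0.48 = 0.52), so the sponsor should accept it knowingly. If the IR-only comparison must be able to stand as confirmatory on its own, use a Holm step-down: test the smaller p-value at 0.025 and, if it is significant, the other at 0.05. That is never less powerful than the equal split now stated. Under Holm the statement in step 4 is still needed.

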### Measures

#### ANS flexibility

ANS flexibility, the primary outcome, will be measured by CAN (central pathway) and HRV (peripheral pathway) at rest and in response to a challenging cognitive stressor, which we term the “stress task.” A protocol comprising rest and a stress task will be conducted within a 3T Prisma MRI scanner with both blood oxygenation level dependent (BOLD) fMRI and MRI compatible ECG monitored simultaneously. All measures for ANS flexibility will be collected at baseline, post-intervention, and 6- and 12-month follow-up.

*Auditory Consonant Trigrams* (ACT) [35, 36], a demanding working memory task, will serve as a cognitive stressor (see task paradigm in Fig. 1). Participants receive a three-consonant trigram (e.g., BME) verbally at a rate of one letter per second, followed immediately by a random three-digit number. Participants are asked to recall the trigram after a time delay (9, 18, or 36 s), during which they performed simple arithmetic aloud (counting backwards from the given number by 3’s) to minimize rehearsal effects. The task consists of five randomized trials for each time delay. The length of the task is 15 min. Before ACT, a 10-min acclimation (rest) period will be administered. We selected ACT as the cognitive stress task due to the high cognitive load that can simulate a cognitively demanding circumstance [35].

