*Analysis of weekly in-lab resting and task-related ECG data*: Degree of similarity between candidate ECG features (sliding window based 2-min segments) and previously revealed ECG shapelet will be calculated for each in-lab session. In our previous study, a higher degree of similarity to the ECG shapelet was related to worse learning from VSOP [11]. Here, we will model the trajectory of degree of similarity across in-lab sessions and calculate the relationship between the slope of trajectory and intervention effects on outcomes. If the combined intervention has greater, additive effects, compared to other groups, on outcomes, we expect to see a stronger relationship between the training process data and changes of main outcomes in the combined intervention group.

Cognition (primary outcome), NPS, IADL, and neurodegeneration (secondary outcomes) will be collected at baseline, post-intervention, and 6- and 12-month follow-up. Blood biomarkers (other outcomes) will be collected at baseline, post-intervention, and 12-month follow-up. All these measures together are considered as the markers of the progress of dementia.

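### Alpha 0.025 covers the two arm comparisons but not the two primary outcomes, and IADL is primary in one section and secondary in another

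*Protocol article*

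**What the plan says.** All places are in the protocol article.

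- **Sample size, outcomes.** The calculation rests on "two primary outcomes (ANS flexibility and cognition/IADL", with the combined arm compared against each of the two control arms.
- **Sample size, alpha.** Alpha is 0.025, and the only purpose given is "correct for two comparisons: combined intervention group with VSOP+IR control, as well as with the IR control group".
- **ANS flexibility, under Measures.** The definition reads "ANS flexibility, the primary outcome, will be measured by CAN (central pathway) and HRV (peripheral pathway) at rest and in response to"; the sentence then names the stress task. No composite and no lead measure is named.
- **Measures, the outcome list after the weekly ECG analysis.** "Cognition (primary outcome), NPS, IADL, and neurodegeneration (secondary outcomes) will be collected at baseline, post-intervention, and 6- and 12-month follow-up". Here IADL is secondary.
- **Measures, Cognition.** One composite of the executive function score, learning and delayed recall is named as the primary measure.
- **Data analysis.** A separate linear mixed model is fitted for each outcome measure. The section gives no significance threshold, no order of testing and no condition that both primary outcomes must be met.

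**The concern.** A Bonferroni split of 0.05 over two arm comparisons protects a single outcome. The article has two primary outcomes, so four primary tests, and the alpha it states leaves the second factor of two unpaid. On the natural reading that a positive result on either outcome is a success, the 5% protection that the correction was meant to buy is not delivered.

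Two features make the primary family less definite still. IADL is joined to cognition as primary where the trial is sized, but is secondary where the outcomes are defined. ANS flexibility has two pathways, each measured at rest and under stress, and none of these is marked as the one on which the claim rests. Both leave room to choose after the results are known. The Blinding section also ties unblinding of the team to completion of the primary-outcome analysis, and that milestone needs a definite list of primary outcomes.

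**Working it through.** **Inputs**

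- Alpha per test 0.025 (Sample size). Sidedness is not stated; two-sided is assumed, so the critical value is 2.241.
- Two comparisons: combined arm against IR+VSOP, and combined arm against IR only (Sample size).
- Two primary outcomes (Sample size).
- Correlation between the two comparisons: 0.5, which follows from the shared combined arm with 38 per group.
- Correlation between ANS measures and cognition: 0.16 (Sample size), taken as the correlation between the test statistics.

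**Step 1: reproduce the stated alpha.** 0.05 / 2 = 0.025, an exact match.

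**Step 2: one outcome, two comparisons.** If independent, 1 − 0.975² = 4.9%; with the shared arm, simulation gives 4.6%. The correction works for a single outcome.

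**Step 3: two outcomes, two comparisons.**

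- Upper bound: 4 × 0.025 = 10%.
- Independent tests: 1 − 0.975⁴ = 9.6%.
- Shared arm and r = 0.16: two multivariate normal simulations gave 9.1% (400,000 draws) and 9.0% (1,000,000 draws).

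**Step 4: does correlation between the outcomes rescue it?** With the shared arm kept and only the outcome correlation changed:

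| Outcome correlation | Family-wise error |
|---|---|
| 0 | 9.0% |
| 0.16 | 9.0% |
| 0.50 | 8.5% |
| 0.70 | 7.9% |
| 0.90 | 6.7% |

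The error stays above 5% throughout, and the article's own correlation is near the top of the table.

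**Step 5: alpha needed for four tests.** An equal split gives 0.05 / 4 = 0.0125 per test (critical value 2.498). The article states no power, so 80% is assumed (normal quantile 0.842):

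- Power at the same size: Φ(2.241 + 0.842 − 2.498) = Φ(0.585) = 72%.
- Size for the same power: ((2.498 + 0.842) / (2.241 + 0.842))² = 1.17, so 96 evaluable participants become about 113.
- If the design had 90% power instead, power falls to about 85%.

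**Step 6: the IADL label.** Sample size puts IADL inside the second primary outcome. The outcome list in Measures puts it with NPS and neurodegeneration as secondary. Both are current text and cannot both hold.

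**The case against.** The strongest reply is that 0.025 appears only as a sample-size input, that the analysis section sets no threshold, and that a hierarchy or joint-success rule is the kind of detail an analysis plan supplies. The hypotheses in the Introduction are also worded jointly, naming ANS indicators together with cognition and everyday function. This is a phase II trial, and whether a mechanistic and a clinical outcome must share one error family is debated.

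Part of this stands. The excess over 5% is conditional: if both outcomes had to succeed, no correction across outcomes would be needed. But the jointly worded hypothesis is not a decision rule. The point also does not rest on silence alone, because the article states the alpha and what it corrects for, and that stated purpose omits one of its own two sources of multiplicity. An analysis plan that imposed an equal split would depart from the alpha on which the trial was sized, and no analysis plan can agree with both IADL labels.

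Some stronger readings are tempting but not supported:

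- **Counting IADL as a third primary outcome, or each ANS measure as its own primary test, and quoting a much larger error.** Sample size counts two primary outcomes, and Measures treats ANS flexibility as one. Nothing says that each component can carry a confirmatory claim. Separate testing would raise the error, but by how much depends on choices the article does not make.
- **Adding the repeated visits as further multiplicity.** Data analysis fits one model per outcome with a visit-by-group interaction, which can be tested once.
- **Taking reactivity as the lead ANS measure already.** The remark that favours reactivity stands in the analysis relating changes in ANS measures to changes in dementia-progress measures. It does not name the endpoint for the treatment comparison.

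**Conclusion.** The point holds in this form. The stated alpha gives 5% protection for one primary outcome, while the article plans on two. If success on either counts, the family-wise error is about 9%. That figure assumes two-sided tests, one test per outcome and comparison, and the article's correlation of 0.16; no outcome correlation in the table brings it down to 5%. Separately, the status of IADL is contradictory as written. That is a labelling error, and it does not cause the 9%.

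**What to change.** 1. **State one rule for the four primary tests.** Any of these keeps the total at or below 5%:
   - Holm over the four tests at overall 0.05.
   - A prespecified order of the two outcomes within each comparison, each tested at 0.025, the second only if the first is significant. The two comparisons then sum to 0.025 + 0.025 = 0.05.
   - A statement that both outcomes must be significant at 0.025 within a comparison for success.
2. **Name one lead measure or one composite for ANS flexibility**, as is already done for cognition. Which one is the investigators' choice.
3. **Change cognition/IADL to cognition in Sample size**, so that it agrees with Measures.
4. **Restate the sample-size alpha and power under the chosen rule.**

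Cost: wording, plus a power consequence that depends on the rule.

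- Holm's strictest step is 0.0125, where an assumed 80% power becomes about 72%; later steps are less strict.
- A fixed order keeps 0.025 but gives up a confirmatory claim on the second outcome when the first fails.
- Joint success keeps 0.025 but lowers the chance of success: with an assumed 80% power per outcome and independence, 0.8 × 0.8 = 64%.

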*Cognition*: Executive function and episodic memory are two primary domains affected earliest by AD-associated neurodegeneration [39]. Executive function will be measured using EXAMINER, a computerized test package designed for RCTs. It includes 8 tests and calculates 4 sub-domain composite scores on working memory (Dot counting and N-back), inhibition (Flanker, Continuous Performance Test, and Anti-saccades), cognitive control (Dimensional Set Shifting), and Fluency (Phonemic Fluency and Category Fluency), and an overall composite score for executive function [40]. Test-retest reliabilities are .78 to .93 [41]. EXAMINER has 3 alternative packages to reduce practice effects and embed basic cognitive process domains (e.g., PS/A) in every task. We do not plan to separately measure these domains using Useful Field of View (UFOV), because UFOV is very similar to VSOP and improves significantly with VSOP [42–44]. Episodic memory will be assessed using the Rey Auditory Verbal Learning [45] and Brief Visuospatial Memory tests [46]. These tests are similar in format, but one focuses on object naming while the other on object shapes, allowing a comprehensive assessment of visual and verbal memory. We chose these standard and validated clinical tests to ensure that our results are comparable to the literature and relevant to practice. We will use alternative forms of the tests to reduce practice effects [47]. The *Z*-transform scores across all assessment points within each test will be developed first to derive 2 composite scores (learning and delayed recall). Both assessments have been validated in MCI and differentiate individuals with MCI from healthy counterparts [45, 46]. A composite score synthesizing EXAMINER composite score, learning, and delayed recall will be created and used as the primary measure for cognition.

*NPS* will primarily be measured using the informant-rated neuropsychiatric symptom inventory (NPI), the full version of 12 domains [48], including both frequency and severity (based on present symptom) scores in the past month.

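### 96 participants do not give 80% power for d = 0.20 in the pairwise comparisons the plan names, even at a between-visit correlation of 0.93

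*Protocol article*

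**What the plan says.** The Sample size section bases the calculation on the combined arm (RFB+VSOP), "by comparing to other groups (IR+VSOP control and IR control only"). The type I error is set for those contrasts: "We estimate alpha = 0.025 (correct for two comparisons: combined intervention group with VSOP+IR control, as well as with the IR control group"). Three measurement times enter: baseline, post-intervention and 12 months. The conclusion is "A sample size of 96 will be able to detect a small effect", quantified as d = 0.20. After an allowance of 20% attrition at 12 months, "we will use a sample size of 114 (*n* = 38 per group").

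The section does not state the power, the sidedness or the between-visit correlation. The only reliability figures are under Measures, Cognition, for the EXAMINER battery: "Test-retest reliabilities are .78 to .93". The Data analysis section plans linear mixed models with the baseline outcome among the fixed effects. It defines its effect sizes with the intra-participant standard deviation.

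**The concern.** The alpha split makes the claim pairwise, so each contrast rests on about 32 against 32. A difference of 0.20 SD is far below what groups of that size usually resolve, and repeated measures close the gap only if visits correlate very highly.

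The sentence is the plan's only statement of what the trial can see. The same section expects a small to moderate effect of VSOP on cognition, and the contrast with IR+VSOP asks what RFB adds to that. If a true increment of 0.20 SD would usually be missed, a reader who takes the sentence at face value will overestimate the trial's sensitivity when the results arrive.

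**Working it through.** **Inputs from the protocol article (Sample size, unless noted).** Alpha 0.025 per comparison; d = 0.20; 96 evaluable, so 32 per arm (equal split inferred from 38 per group); baseline plus two follow-ups; 114 enrolled; 20% attrition. Reliability .78 to .93 is from Measures, Cognition.

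**Assumptions, not in the document.** Two-sided test; 80% as the benchmark; d in single-visit SD units; equal correlation ρ between all visits; ρ from 0.5 to 0.93.

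**Step 1: try to reproduce 96.** Without repeated measures, n per arm = 2(2.241 + 0.842)²/0.20² = 476 for 80% power, or 3 × 476 = 1,428 in all. At 32 per arm, power is 7%.

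Repeated measures multiply n by the variance factor v of the contrast, where v is:
- change from baseline to the mean of two follow-ups: v = 1.5(1 − ρ)
- mean of two follow-ups, baseline-adjusted: v = (1 + ρ)/2 − ρ²

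At ρ = 0.78, v is 0.330 or 0.282, giving 157 or 134 per arm. At ρ = 0.93, v is 0.105 or 0.100, giving 50 or 48 per arm. None of these is 32.

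**Step 2: power at 32 per arm.** SE = √(2v/32); noncentrality = 0.20/SE; critical value t(62) = 2.297.

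| ρ | Change: SE | Power | Adjusted: SE | Power |
|---|---|---|---|---|
| 0.5 | 0.217 | 9% | 0.177 | 13% |
| 0.7 | 0.168 | 14% | 0.150 | 18% |
| 0.78 | 0.144 | 19% | 0.133 | 22% |
| 0.93 | 0.081 | 57% | 0.079 | 59% |

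**Step 3: correlation needed for 80%.** The effect must be about 3.145 SEs, so SE = 0.20/3.145 = 0.0636 and v = 16 × 0.0636² = 0.0647. For change from baseline, 1 − ρ = 0.0647/1.5 = 0.043, so ρ is about 0.957. With baseline adjustment it is about 0.956.

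**Step 4: more favourable readings, at ρ = 0.93.**
- One-sided alpha 0.025, 32 per arm: 68% (change), 70% (adjusted).
- Two-sided, all 38 per arm retained: 66%, 68%.
- Both together: 76%, 78%.

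**Step 5: the evaluable number.** 114 × 0.80 = 91.2, and 91.2/3 = 30.4 per arm. Keeping 96 after 20% loss needs 96/0.80 = 120 enrolled. Going from 114 to 96 is a loss of 18/114 = 15.8%. At 30 per arm and ρ = 0.93, power for d = 0.20 falls to 54% (change) or 56% (adjusted).

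**Step 6: what 30 per arm can detect.** Baseline-adjusted, 80% power needs about 3.15 × √(2v/30):
- ρ = 0.7: 3.15 × 0.155 = 0.49 SD
- ρ = 0.78: 3.15 × 0.137 = 0.43 SD
- ρ = 0.93: 3.15 × 0.082 = 0.26 SD

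**The case against.** **The power range is not a property of the document.** This stands. It depends on the assumed correlations and on the model. Other reasonable two-sided models, including one visit or three, span about 7% to 67%, still below 80%. Stacking every favourable choice can pass 80%: one-sided testing, no dropout, ρ = 0.93 and all three follow-ups give v = (1 + 2ρ)/3 − ρ² = 0.088 and noncentrality 0.20/√(2 × 0.088/38) = 2.93. Against a critical value of 1.99 that is roughly 83%. But the plan's calculation counts two follow-ups and allows for 20% loss, so this is not the case it describes.

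**The reliability range is a loose benchmark.** Also true. It covers EXAMINER only, not the memory tests, the cognition composite or the ANS measures, and test-retest reliability is not a 12-month correlation. A correlation above 0.95 is therefore not disproved. Nothing in the document supports one.

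**The SD scale is assumed.** The Data analysis section scales effects by the intra-participant SD. On that scale, change-score power for 0.20 is about 5% to 6%, so the objection does not help the claim.

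**An article may leave power and correlation to a fuller document.** Agreed, and their absence is not the point. The point is a stated numerical claim.

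**Two stronger readings should be resisted.** A reader might infer that the plan promises a null result will exclude a small effect. It says only that the sample can detect one, and it plans effect sizes with 95% confidence intervals, which would show the imprecision. A reader might also infer that Cohen's f was relabelled as d. An omnibus three-group, three-visit interaction test with f = 0.10, N = 96, alpha 0.025 and ρ = 0.8 has noncentrality 96 × 0.01 × 3/0.2 = 14.4 and 79.7% power. There f = 0.10 means a sustained difference of about 0.42 SD (two arms, f = d/√18) to 0.45 SD (three arms, f = 2d/9). The match needs an assumed ρ, and the document names no test, formula or software, so this is a possible cause only.

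**Conclusion.** The d = 0.20 claim is wrong as written for the stated pairwise comparisons, judged at 80% power. Under the listed assumptions, power runs from about 9% to 59% across the two models, and the claim becomes true only at a correlation of about 0.956 or more. Neither one-sided testing nor full retention of 38 per arm rescues it at ρ = 0.93.

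The attrition arithmetic is a second, smaller error in the same section: the enrolled number and the stated loss leave about 91, not 96. The finding concerns what the plan says the trial can detect. It does not show that the design, the analysis model or the enrolment target must change.

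**What to change.** Delete the d = 0.20 claim, reconcile 96, 114 and 20%, and state the detectable difference with its power, alpha, correlation and SD scale. Possible wording:

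> With about 30 evaluable per arm (114 enrolled, 20% attrition), two-sided alpha 0.025 per comparison and an assumed between-visit correlation of 0.7, the trial has 80% power for a baseline-adjusted difference of about 0.49 single-visit SD, averaged over two follow-ups, between RFB+VSOP and each control (0.43 SD at a correlation of 0.78, 0.26 SD at 0.93).

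If the team holds correlation data for the ANS and cognition outcomes, those values should replace the assumed 0.7. If the figure of 96 came from an omnibus test on another effect scale, name that test and scale. The cost is wording only, with no added participants. The downside is that the stated detectable effect becomes less favourable.

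### Randomising 114 does not preserve 96 participants at 12 months under the plan's own 20% attrition; that needs 120, or attrition of at most 15.8% (a minor correction)

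*Protocol article*

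**What the plan says.** The Sample size section of the protocol article builds the number in three steps.

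- Required number: "A sample size of 96 will be able to detect a small effect", given as d = 0.20. The calculation uses alpha = 0.025 to allow for two comparisons and "3 measurement time points: baseline, post-intervention assessment, and 12-month follow-up".
- Loss: "We further estimate a 20% attrition rate at the 12-month follow-up". The support offered is a local cohort of cognitively healthy older adults that lost under 20% over as long as five years.
- Result: "and we will use a sample size of 114", which is 38 in each of three groups.

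The Abstract and the Trial design section repeat 114. No other attrition rate is given, and no reason for choosing a number below 120. The Data analysis section specifies intention-to-treat linear mixed models over baseline, post-intervention, 6 months and 12 months, with a random participant effect.

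**The concern.** The attrition sentence follows directly on the 96, introduces a further allowance, and ends in the larger number. The natural reading is that 96 is what the calculation needs once losses have occurred and that 114 is 96 inflated for 20% loss. On that reading the inflation is too small: the plan's own rate applied to its own 114 does not return 96.

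What is at stake is the sample-size justification. The stated detectable effect rests on 96, while the plan's own assumption implies fewer than 96 at the 12-month visit, which is one of the visits the calculation names.

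**Working it through.** **Inputs, all from the Sample size section**

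- Number needed: N = 96, which is 96/3 = 32 per group
- Attrition at 12 months: a = 0.20
- Number randomised: 114, which is 38 per group

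**Step 1. Try to reproduce 114.** To keep N after a fraction a is lost, randomise N/(1 - a).

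- Total: 96/(1 - 0.20) = 96/0.80 = 120
- Per group: 32/0.80 = 40

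The stated 114 is 120 - 114 = 6 below this, or 5%. It is not reproduced.

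**Step 2. What would give 114?** Multiplying by (1 + a) per group gives 32 x 1.20 = 38.4. Rounded down, that is 38, and 38 x 3 = 114. The same multiplication on the total gives 96 x 1.20 = 115.2, which is not 114. So 114 fits a multiplication in place of a division only if it was done per group and rounded down. The document does not show its working, so this origin is a guess.

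**Step 3. What does 114 leave at 12 months with 20% loss?**

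- Total: 114 x 0.80 = 91.2, about 91
- Per group: 38 x 0.80 = 30.4, about 30, against 32
- Shortfall: 96 - 91 = 5 participants

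**Step 4. What attrition does 114 allow?** 1 - 96/114 = 0.158, or 15.8%.

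**Step 5. Effect on sensitivity.** With power and alpha held fixed, the detectable standardised effect scales with 1/sqrt(N). The ratio is sqrt(96/91) = 1.027, so d = 0.20 would become about 0.20 x 1.027 = 0.205. This treats everyone lost by 12 months as contributing nothing, so about 3% is an upper limit.

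**What cannot be checked.** The section does not state power, sidedness or the within-person correlation. The 0.205 is therefore a scaling of the plan's own 0.20, not an independent calculation of the detectable effect. Steps 1 to 4 do not depend on those inputs.

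**The case against.** The strongest reply is that the planned analysis does not need complete cases. The calculation uses three time points, the 20% applies only to the last, and the mixed model keeps whatever earlier visits a participant provides. Someone lost late in follow-up still contributes baseline, post-intervention and perhaps 6-month data. The document also never says that 96 means participants who complete 12 months. If 96 is merely the number entering a model that tolerates missing visits, then 114 is a partial allowance rather than a strict contradiction.

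Much of this stands. It makes the loss of information smaller than the head count suggests, and it means that the 120 rests on reading the sentences in sequence. It does not restore 96 participants at 12 months. Nor does the section say that 114 was chosen as a partial allowance; it ties the allowance to the 12-month visit and gives a single rate.

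Three stronger inferences are tempting and are not supported.

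- **That 20% is optimistic for people with MCI because the reference cohort was cognitively healthy.** The documents give no attrition figure for MCI. The cohort's rate of under 20% covered up to five years, and the plan applies 20% to a trial of about 14 months, so it already allows for faster loss than its source. The section on feasibility of the self-administered intervention also sets out retention measures.
- **That a multiplication error has been shown.** It is a plausible origin and no more.
- **That the shortfall undermines the trial.** Five participants and at most a 3% change in the detectable effect alter no comparison or design feature.

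**Conclusion.** The point holds as a minor error in a stated figure. On the plan's own inputs, 96 after 20% loss requires 120 randomised (40 per group). The planned 114 leaves about 91 at 12 months (about 30 per group), and it is consistent with 96 only if attrition is at most 15.8%.

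The conclusion assumes that 96 is the number wanted after attrition, which the order of the sentences supports but no sentence says outright. The upper limit on the effect also assumes that the detectable difference scales with the square root of the sample size.

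**What to change.** Keep 114 and correct the sentence that links it to 96. Either wording would do:

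- 'A total of 114 (38 per group) allows for about 16% (15.8%) attrition at 12 months while retaining 96.'
- 'With 20% attrition, about 91 of 114 (about 30 per group) are expected at 12 months.' The detectable effect should then be restated on that number, using the authors' own power, sidedness and correlation inputs.

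If the second wording is used, a short clause can add that participants lost by 12 months contribute their earlier visits to the mixed model.

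The cost is one sentence. The second wording also means rerunning the existing calculation and accepting a slightly less favourable figure. Recruitment, allocation and analysis are unchanged.
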